**Study Population**

Approximately 112 subjects will be randomized and considering 10% drop-out, the final evaluable subjects shall be 100.

**Subject Eligibility Criteria**

**Inclusion Criteria**

This study targets infectious subjects normally associated with treatment in hospital setting. The following main criteria for inclusion must be met for study entry:

1. Patients of both sexes aged from 18 years to 60 years old.
2. Willing and able to provide written informed consent prior to performing study procedures by the subject or legal guardian willing and able to provide written informed consent prior to performing study procedures
3. Patients with Severe Acute Respiratory Syndrome Coronavirus (SARS-CoV)-2 infection confirmed by RT Polymerase chain reaction (RT-PCR) test between 1 and 120 Hours before randomization
4. Currently hospitalized and requiring medical care for COVID-19
5. Peripheral capillary oxygen saturation (SpO2) > 94% on room air at screening
6. Radiographic evidence of pulmonary infiltrates

**Exclusion Criteria**

Candidates for the study will be excluded if ANY of the following criteria are present:

1. Subject or Authorized Representative is unable to provide informed consent
2. Subject is pregnant or breastfeeding ladies
3. Subject is of childbearing potential and has a positive pregnancy test since admission to the hospital
4. Subject is < 18 years of age
5. Subject has a known allergy to herbal compounds or ZingiVir-H or any components of the drug product
6. Subject has had previous treatment with ZingiVir-H
7. Body weight ≥ 175 kg
8. Intra-thoracic or intra-abdominal surgery within the 12 hours prior to consent, or ongoing impairment of hemostasis as a result of one of these procedures
9. A history of head trauma, spinal trauma, or other acute trauma with an increased risk of bleeding.
10. Cerebral Vascular Accident (CVA) or Intracerebral Arteriovenous Malformation (AVM), cerebral aneurysm, or mass lesions of the central nervous system or melena, hematemesis.
11. Inability to take oral medication
12. Prolonged QTc-interval in baseline ECG (>500 ms)
13. History of solid organ, allogeneic bone marrow, or stem cell transplantation.
14. Severe renal failure characterized by chronic or acute need of hemodialysis, hemofiltration or peritoneal dialysis
15. Need of anticoagulants, antiplatelet agents, antithrombotics and thrombolytics during the treatment period.
16. Participation in another research study involving an investigational agent within 30 days prior to consent

**Criteria for Discontinuation from Study Drug or Study Participation**

**Withdrawal from receiving study drug**

A subject may remain in the study but discontinue the administration of study drug at any time during treatment. Reasons for this may include:

- Intolerable adverse event(s)
- Subject’s request
- Investigator’s judgment (e.g. related SAE)
- Administration of study drug is contraindicated if the co-administration of standard of care medication which is required for subject treatment.
- Need for mechanical intubation due to respiratory failure (Hypecapnic)

In any above case of withdrawal or lost to follow-up on the patients status shall be document as appropriate in the patient source document and needs to be reported as appropriate to sponsors.

**Investigational Product, manufacturing, Dosage and Mode of Administration: ZingiVir-H**

The study drug ZingiVir-H is a poly herbo-mineral formulation, which is a blend of antiviral phyto-molecules and processed purified and detoxified form of natural metallic compounds. It is a unique combination of Lavanga (Eugenia caryophyllus), Ardraka (Zingiber officianale), Mustha (Cyperus rotundus), Parpataka (Hedyotis corymbosa), Ajamoda (Trachyspermum ammi), Hingula (Cinnabar, HgS), Haratala (Arsenic trisulphide) and Pharmaceutical grade starch. Even though the study drug contains minerals such as HgS and As2S3 their dose is designed in such a way that there is no cumulative dose sufficient for making any type of toxicity in the continuous usage for maximum of 15 days. The drugs in the combination have showed marked antiviral, antipyretic and immunomodulatory effects.

**Therapeutic dose**:

ONE tablet (500 mg each consumed once in 3 hours ±1 hour between 6 AM and 9 PM in a given day (6AM, 9AM, 12Noon, 3PM, 6PM, 9PM) for a minimum duration of 10 days to Maximum 15 days continuously as per the clinical conditions and disease outcome. Compliance on study drug consumption is important to evaluate the study endpoints.

**Masking:**

Quadruple (Participant, Care Provider, Investigator, Outcomes Assessor)

**Duration of Treatment**: Minimum of Ten days to Maximum of Fifteen (15) days of study drug regimen and a follow-up on 30^th^ day from the day of baseline.

**Reference Therapy, Dosage and Mode of Administration**: Placebo and Standard of Care (SOC)

Placebo for this study is supplied as identically labeled, tablets. Placebo will also be required to be maintained in controlled environment as IP. Placebo must be consumed according to the same procedures and guidelines as ZingiVir-H.

**Blinding**

Study drug will be assigned and administered in a Single blind fashion.

In the event of a medical emergency where it is imperative to know which treatment arm the subject was randomized to in order to make future treatment decisions, the Investigator may break the blind for an individual subject after getting approval from study monitor or sponsor. If any adverse events causing the need for subject unblinding, will be handled as a serious adverse event in accordance with the procedures outlined in this protocol. Any broken blind will need to be clearly justified, explained by a comment within the Case Report Form (CRF), and captured on the Serious Adverse Event Form.

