**Protocol Synopsis**

**Title of Study:** Randomized controlled Single blinded prospective multi centre clinical trial to investigate the safety and efficacy of ZingiVir-H as an adjuvant therapy in hospitalized adults diagnosed with coronavirus disease 2019 (COVID-19).

**Name of Sponsor/Company:** Pankajakasthuri Herbal Research Foundation, Thiruvananthapuram, Kerala, India

**Name of Investigational Product:** ZingiVir-H

**Name of Active Ingredient:** Herbal ingredient extracted from Lavanga (*Eugenia caryophyllus*), Ardraka (*Zingiber officianale*), Mustha (*Cyperus rotundus*), Parpataka (*Hedyotis corymbosa*), Ajamoda (*Trachyspermum ammi*), Hingula (Cinnabar, HgS), Haratala (Arsenic trisulphide)

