**Primary Efficacy Endpoint:**

The Odds of Ratio for Improvement on a 7-point Ordinal Scale on Day 15 [Time Frame: Day 15 from the day of study inclusion]. The odds ratio represents the odds of improvement in the ordinal scale between the treatment groups. The ordinal scale is an assessment of the clinical status at a given day. Each day, the worst score from the previous day will be recorded.

The scale is as follows: 1. Death 2. Hospitalized, on invasive mechanical ventilation or Extracorporeal Membrane Oxygenation (ECMO) 3. Hospitalized, on non-invasive ventilation or high flow oxygen devices 4. Hospitalized, requiring low flow supplemental oxygen 5. Hospitalized, not requiring supplemental oxygen - requiring ongoing medical care (Coronavirus (COVID-19) related or otherwise) 6. Hospitalized, not requiring supplemental oxygen - no longer required ongoing medical care (other than per protocol ZingiVir-H administration) 7. Discharge from hospital.

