**INVESTIGATIONAL PLAN**

**Overall Study Design**

This is a Randomized controlled, single blinded multi-center, comparative study of ZingiVir-H as an adjuvant therapy in hospitalized adults diagnosed with coronavirus disease 2019 (COVID-19). At inclusion, subjects who meet all inclusion criteria and no exclusion criteria will be assigned, in either therapeutic arm (ZingiVir-H), to receive ZingiVir-H in a dose of 500 mg tablet each consumed once in 3 hours ±1 hour between 6 AM and 9 PM in a given day (6AM, 9AM, 12Noon, 3PM, 6PM, 9PM) for a minimum duration of 10 days to Maximum 15 days OR will be on a Placebo arm to receive placebo (without active ingredients) each consumed once in 3 hours ±1 hour between 6 AM and 9 PM in a given day (6AM, 9AM, 12Noon, 3PM, 6PM, 9PM) for a minimum duration of 10 days to Maximum 15 days. The allocation of study arm is strictly as per the discretion of the Investigator. Whereas both the study groups shall be given standard of care of treatment as per the research site policies or COVID-19 therapeutic management policies. These doses will be administered orally. Blood samples for assessing CBC; safety laboratory tests and immunomodulatory markers will be obtained between baseline assessments (Day-01), during the day-06 of inclusion, at the end of the treatment day-15 and at the end of the study day-30. Safety-related assessments will include reports of adverse events and clinical laboratory test results.

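### The protocol calls the trial single blind in some sections and quadruple masked in others, so the primary ordinal scale may be scored by someone who knows the arm

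*Protocol*

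**What the plan says.** Single blind appears in three kinds of place:

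- The title, given in the Protocol Synopsis and repeated after its Statistical Methods entry: "Randomized controlled Single blinded prospective multi centre clinical trial".
- Overall Study Design: "This is a Randomized controlled, single blinded multi-center, comparative study of ZingiVir-H".
- Blinding: "Study drug will be assigned and administered in a Single blind fashion".

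Four-party masking appears in two, the Masking entry of the synopsis and the Masking entry of the body: "Quadruple (Participant, Care Provider, Investigator, Outcomes Assessor"). The entry in the body stands just before the Blinding section.

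Two further statements bear on what the investigator knows. The Blinding section says that in a medical emergency "the Investigator may break the blind for an individual subject after getting approval from study monitor or sponsor". Overall Study Design says "The allocation of study arm is strictly as per the discretion of the Investigator".

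The primary endpoint is "The Odds of Ratio for Improvement on a 7-point Ordinal Scale on Day 15". Category 6 of that scale is "Hospitalized, not requiring supplemental oxygen - no longer required ongoing medical care (other than per protocol ZingiVir-H administration"), and category 7 is discharge. Ordinal Scale assessment requires daily scoring but does not say who does it.

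**The concern.** Single blind normally means that only the participant is unaware of the arm. Quadruple masking names four parties, among them the investigator and the outcomes assessor. One trial cannot be both. With up to 5 sites, two sites could run different blinding and each could point to the protocol for it.

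The primary endpoint is exposed to this. A scale whose outcome turned only on death or ventilation would suffer little from an unblinded scorer. Here the decisive steps are whether a patient still needs medical care and whether the patient goes home. If the person making or recording those judgements knows the arm, the primary odds ratio can move without any drug effect, and no analysis can repair that afterwards.

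**Working it through.** **Step 1. The blinding statements side by side.**

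| Place in protocol | What it states or implies |
|---|---|
| Title | Single blind |
| Overall Study Design, opening sentence | Single blind |
| Blinding, opening sentence | Single blind; blinded party not named |
| Masking (synopsis and body) | Participant, care provider, investigator and outcomes assessor all masked |
| Blinding, emergency text | Investigator needs approval to break the blind; most naturally read as a blinded investigator |
| Overall Study Design, allocation sentence | Investigator decides the arm; implies an investigator who knows it |

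The last two rows pull in opposite directions, so the rest of the text does not resolve the conflict.

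**Step 2. Does it reach the primary endpoint?** The Inclusion Criteria require current hospitalization, a need for medical care for COVID-19 and SpO2 above 94% on room air. That profile matches category 5 (in hospital, no supplemental oxygen, care still needed). Most patients should therefore start there, although the scale records the previous day's worst score, so a few may enter lower. From category 5, improvement means 6 or 7. The boundary between 5 and 6 is a judgement about need for care, and 7 follows a discharge decision. Categories 1 to 4 are more objective, but they are not where most patients start.

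**Step 3. What could a scoring shift do?** The protocol gives no figure to reproduce here: it states no improvement rate and no effect size. What follows is illustration only.

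Inputs from the protocol: 100 evaluable subjects and 1:1 allocation, so 100/2 = 50 per arm; Fisher's exact test for categorical comparisons.

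Assumptions not in the protocol: improvement treated as yes/no, the same true rate in both arms, and upgrades only in the active arm.

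Odds ratio = [a/(50 − a)] / [b/(50 − b)], where a and b are the numbers scored improved on active and placebo.

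| True rate, both arms | Active patients upgraded | a v b | Odds ratio | Fisher p |
|---|---|---|---|---|
| 35/50 | 5 | 40 v 35 | (40/10)/(35/15) = 1.71 | 0.36 |
| 35/50 | 8 | 43 v 35 | (43/7)/(35/15) = 2.63 | 0.09 |
| 35/50 | 9 | 44 v 35 | (44/6)/(35/15) = 3.14 | 0.048 |
| 35/50 | 10 | 45 v 35 | (45/5)/(35/15) = 3.86 | 0.023 |
| 45/50 | 5 (all remaining) | 50 v 45 | not finite (50/0) | 0.056 |

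At 35/50 there are 50 − 35 = 15 non-improvers on active, so reaching p < 0.05 means upgrading 9/15 = 60% of them.

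**Step 4. The same question as an error rate.** Exact binomial enumeration of the two-sided Fisher test at 0.05, with 50 per arm, no drug effect and true rates of 50%, 60%, 70% and 80%:

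| Assumed scoring shift towards active | False-positive rate across those true rates |
|---|---|
| none | 2.8% to 3.5% |
| 5 percentage points | 5.4% to 6.0% |
| 10 percentage points | 13% to 20% |
| 15 percentage points | 27% to 51% |

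**The case against.** A reader might infer that the protocol has an unblinded investigator scoring the primary endpoint. It does not say so. The blinded party under single blind is never named, and neither is the scorer. The Masking entries and the emergency text suggest that wider blinding may have been intended. The risk is therefore conditional on a site reading single blind in its usual sense and on the scorer being someone who then knows the arm.

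A reader might also say that the Blinding section contradicts itself outright, because only a blinded investigator could break a blind. That is the more natural reading, but the wording could also describe disclosing the arm of a blinded subject. It counts as a pointer, not as proof.

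Nor does the protocol give discharge criteria or say who applies them. Standard of care follows site or COVID-19 management policies, which may limit individual discretion. And the illustration shows no expected size of bias: a nominally significant result from a single typical outcome needs gross mis-scoring at a 35/50 base rate, and at 45/50 even the maximum upgrade falls short.

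These objections limit how strongly the consequence can be put. They leave untouched the conflict between single blind and four-party masking, which is on the face of the current text and not explained elsewhere in it. Who is blinded is also a matter for the protocol itself, because it decides packaging, code custody and who may assess outcomes.

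**Conclusion.** The protocol contradicts itself on who is blinded, and this must be corrected before enrolment. That conclusion rests on the text alone and needs no assumption.

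The consequence is conditional: under the participant-only reading, the primary scale may be scored with knowledge of the arm, and the primary odds ratio is then open to assessor bias. The direction of the threat is clear; its size cannot be derived from the document. Under the assumptions shown, a shift of 5 percentage points takes the false-positive rate only slightly above the nominal 5%, while 10 points takes it to 13% to 20%. Those figures depend on assumed base rates and a yes/no reading of improvement, and should not be cited as an estimate of the bias in this trial.

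**What to change.** Bring the title, both Masking entries, Overall Study Design and Blinding to one statement. The four-party masking already in the protocol is the version to keep, since it protects the primary endpoint and a placebo is already planned. Specifically:

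1. Replace single blind wherever it occurs (both appearances of the title, Overall Study Design, Blinding) with a statement that participant, care provider, investigator and outcomes assessor are blinded.
2. In Ordinal Scale assessment, name the role that scores the scale and state that this person is blinded.
3. State that the code is held by someone outside the treating team.
4. Remove the sentence that leaves allocation to the investigator's discretion. Blinding the investigator cannot work while it stands.

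The emergency code-break procedure is a separate matter, and no change to it is proposed here.

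The cost is amendment wording, coded packs, and pack handling by someone outside the treating team. One check is needed first. The protocol says only that the placebo tablets are labelled identically; it does not say that they match in appearance, taste or smell, and the active product contains clove and ginger. The sponsor should confirm that the two are indistinguishable, because otherwise the masking would hold only on paper.

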**Visit Schedule and Assessments**

**Screening / Randomization Visit – Day 01**

Subjects must meet the inclusion criteria and have none of the exclusion criteria in order to be eligible for randomization in this study. Subjects who meet all eligibility criteria, and have signed informed consent will be discussed randomize and move on to the Baseline study visit. Once the subject is randomized the sponsor representative or the study Investigator will provide the study staff with a unique randomization number for the subject.

Following assessments must be made at this Baseline visit for each study subject:

- RT-PCR test assuring the subjects test positive for COVID-19.
- Demographics
- Medical history (all known information regarding the subject’s health history/relevant surgeries/interventions prior to signing the informed consent).
- Vital signs: Body temperature, Pulse – beats per minute (BPM), Blood Pressure (BP) mmHg, Respirations – breaths per
- Concomitant medications (including medications, fluids and blood products administered within the 7 days prior to randomization).
- Documentation of any other infection if available (site of infection and, if available: positive culture results, prior antibiotics, sensitivity of cultured organism to antibiotics, nonmedical treatment such as surgery or drainage).
- Physical Examination including the following: general appearance, Head, Eye, Ear Nose Throat (HEENT), neck, respiratory, cardiovascular, chest, abdomen, lymphatic, musculoskeletal and extremities, skin and neurologic examination. Height and weight (baseline dry weight).
- Blood will be obtained for following laboratory tests:
  - Complete Blood Count with differential (Hemoglobin, Hematocrit, and WBC with differential count) & ESR
  - Serum Chemistry- Creatinine, Urea, CRP, ALT, AST, Alkaline Phosphatase, Albumin, total bilirubin
  - Pregnancy test; Serum or Urine human Chorionic Gonadotropin (hCG) - Pregnancy test only required for woman of childbearing potential on the day of randomization
  - Immunomodulatory markers, IL6, IL7, Interferon α, IgG, IgM

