**Data Management**

**Documentation**

Case report forms (CRFs) will identify each subject by subject number (compilation of site number and randomization number) and subject's initials (per local regulatory guidelines). Originals or copies of all source documents, and correspondence will be kept on file at the investigational site.

The data required by the protocol will be recorded in the appropriate pages of CRFs. All source data will be available to the study monitor who may perform a 100% data check (comparison of the data recorded in the eCRF with those in the source documents). The source data will also be available for an audit by the Sponsor and all applicable regulatory agencies at any time.

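### Emergency unblinding needs prior approval from the monitor or sponsor, with no time limit or fallback; the step is a barrier if the investigator is masked and has no function if only the participant is

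*Protocol*

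**What the plan says.** The Blinding section opens with "Study drug will be assigned and administered in a Single blind fashion". It then sets out when the code may be broken: "In the event of a medical emergency where it is imperative to know which treatment arm the subject was randomized to", for the purpose of later treatment decisions. In that case, "the Investigator may break the blind for an individual subject after getting approval from study monitor or sponsor". The section states no time limit for the approval and no alternative if approval cannot be had.

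The same section requires every code break to be justified, explained in a comment in the case report form and recorded on the serious adverse event form. The Serious Adverse Events section adds that an adverse event that makes unblinding necessary is handled as serious, and that the form goes to the sponsor within 24 hours.

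The protocol describes who is blinded in two ways:

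- The Masking entry, in the synopsis and again in the body directly before the Blinding section, reads "Quadruple (Participant, Care Provider, Investigator, Outcomes Assessor".
- The study title and the Overall Study Design section say single blind; the latter states "This is a Randomized controlled, single blinded multi-center, comparative study of ZingiVir-H as an adjuvant therapy".

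The Overall Study Design section also says "The allocation of study arm is strictly as per the discretion of the Investigator".

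**The concern.** An emergency unblinding rule exists so that a treating investigator who does not know the arm can learn it when the knowledge is needed at once. Making that depend on agreement from someone outside the site, with no time limit and no fallback, works against its purpose. At stake is the time a masked investigator may wait for information that the section itself calls imperative. The subjects are hospitalised COVID-19 patients and respiratory failure is a listed safety endpoint, so emergencies are foreseeable.

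The rule also takes for granted that the investigator is blinded. The protocol does not say so consistently, and a site cannot tell from the text whether the procedure applies to its investigator at all.

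**Working it through.** No arithmetic applies: the protocol gives no expected number of code breaks and no approval time. The check sets the passages side by side.

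**Step 1. What triggers the rule.** The Blinding section limits it to a medical emergency in which the arm must be known. No non-urgent category is described to which an approval step might have been meant to apply.

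**Step 2. What the rule requires.** Approval by the monitor or the sponsor comes before the code is opened. Delay is an inference, not a statement in the text. It follows from a mandatory prior step that has neither a deadline nor a substitute.

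**Step 3. What the rule does under each description of the blinding.**

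| Reading | Where it stands | Is there a blind for the investigator to break? | Effect of the approval step |
|---|---|---|---|
| Investigator masked | Masking entries, synopsis and body | Yes | A barrier between the investigator and the code during an emergency |
| Single blind in the usual participant-only sense | Study title, Overall Study Design, Blinding | No | None; the step has no function |

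The two effects are alternatives and cannot hold together. The protocol never says which role its single-blind label covers, so the text alone does not settle which row applies. The procedure in the Blinding section fits the first row, while that section's own opening sentence, in its usual meaning, fits the second.

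**Step 4. What the allocation text adds.** Allocation at the investigator's discretion, in the Overall Study Design section, points towards an investigator who knows the arm. The Screening / Randomization Visit section says instead that "the sponsor representative or the study Investigator will provide the study staff with a unique randomization number for the subject", which describes the issue of a number and does not say that its issuer knows the arm. The discretion sentence is hard to square with a masked investigator and must be reconciled along with the rest.

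**Step 5. What would be lost without prior approval.** The written justification, the case report form comment and the serious adverse event form all follow the code break and do not depend on approval. The sponsor already has a 24-hour reporting route. Accountability therefore remains; what goes is control in advance.

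**The case against.** The strongest reply is that the sentence refers to future treatment decisions, that approval might be given in minutes, and that a sponsor may reasonably want to prevent needless code breaks. It is true that the text shows no actual delay. But the trigger is an emergency with an imperative need to know, and nothing in the section makes approval quick. Needless code breaks are already discouraged by the required justification and reporting.

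Four stronger readings are tempting, and the documents do not support them.

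- *That the investigator already knows the arm.* A reader might infer this from the single-blind label and the discretion sentence. The protocol nowhere states it, and the Masking entries say the opposite. If it were so, the approval step would delay nothing.
- *That approval spreads knowledge of the arm to people who review the data.* The monitor's role might suggest it: "All source data will be available to the study monitor who may perform a 100% data check". Yet approval precedes the code break and need not reveal the arm. No passage lists the monitor or sponsor as masked.
- *That no approver can be reached out of hours.* Contact pages are not in the text available for this review, and the Serious Adverse Events section refers to contact information supplied for safety reporting. Only the missing time limit and fallback in the Blinding section can be asserted.
- *That patient safety as a whole hangs on the approval.* The section on withdrawal from study drug lets administration be discontinued at any time, including on the investigator's judgment, and states no need for approval or unblinding. The approval step governs only knowledge of the arm.

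It is also fair to say that the conflict between single blind and quadruple masking is a wider defect than this one rule. It belongs here only because it decides whether the rule is harmful or empty.

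**Conclusion.** The point stands in a limited form. The protocol fixes an emergency unblinding rule that serves badly if followed: it is an avoidable barrier if the investigator is masked, and without function if only the participant is blinded. This is a rule the protocol states, not a detail left to another document.

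Its size cannot be expressed as a number. The consequence falls on individual subjects who need an emergency code break, and is limited to the time taken to learn the arm. Nothing in the documents shows an effect on the primary analysis.

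The conclusion rests on two assumptions: that single blind carries its usual participant-only meaning where the protocol uses it without definition, and that no time limit or fallback stands elsewhere in text not available here. If such a provision exists, the first reading becomes less serious, but the contradiction over who is masked remains. The change is worth making because it is cheap and gives a specific gain for patient safety.

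**What to change.** In the Blinding section, let the investigator open an individual subject's code in a medical emergency without prior approval, then notify the monitor or sponsor promptly, within a time the protocol states and without giving the arm where possible. Keep the justification, the case report form comment and the serious adverse event reporting as they stand. This concerns access to the code only and sets no rule on how a patient is treated.

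At the same time, state by role who is blinded, and bring into line the Masking entries (synopsis and body), the study title, the Overall Study Design section, the opening sentence of the Blinding section and the sentence leaving allocation to the investigator's discretion. If the investigator is in fact not masked, the emergency procedure should be rewritten to say whose blind it breaks.

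The cost is a sentence or two in the protocol and sealed or electronic code access held at each of the up to 5 sites. The downside is that the sponsor gives up control in advance over code breaks and relies on review afterwards.
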